#### Single-Blind Design

A single-blind design will be maintained. Veterans will know that they will be receiving sham and active rTMS but will not know when they are receiving which treatment. The consent form will specify that they will be blinded to treatment order. The biostatistician will be blinded to group. Researchers will be unblinded to treatment order because all participants receive sham rTMS first and active rTMS second. This is necessary because the “washout” period of rTMS effects is unknown, and objective 2 examines sustainability.

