### rTMS Intervention

#### Randomization to Stimulation Site Group

Veterans with AUD+mTBI will be randomly assigned to 1 of 2 stimulation site groups: a customized site or left DLPFC. SAS 9.4 (SAS Institute Inc) will be used to develop the randomization protocol for the veterans, ensuring an equal number of participants—assigned sequentially—in each of the 2 groups. An electroencephalography (EEG) cap along with the coordinate Beam F3 method and neuronavigation will be used for each participant to maintain the single-blind design. The randomization scheme will be provided by the biostatistician to a single unblinded administrator (who will not complete any research procedures or analyses). This administrator will inform the rTMS provider of the patient’s assigned site (left DLPFC or a customized site) for rTMS treatment.

The customized site will be one of the sites depicted in Figures 1- 3- as determined by ongoing analyses.

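### The biostatistician hands over the randomisation scheme yet is declared blinded to group: analyst blinding is asserted but not secured

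*Protocol article*

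**What the plan says.** All of this is in the protocol article.

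- **What group means** (Randomization to Stimulation Site Group): "Veterans with AUD+mTBI will be randomly assigned to 1 of 2 stimulation site groups: a customized site or left DLPFC".
- **How the scheme is built** (same section): "SAS 9.4 (SAS Institute Inc) will be used to develop the randomization protocol for the veterans, ensuring an equal number of participants". The section then specifies sequential assignment. The person who runs the program is not named.
- **Who hands it over** (same section): "The randomization scheme will be provided by the biostatistician to a single unblinded administrator". The recipient is said to take no part in procedures or analyses.
- **Who then learns the site** (same section): "This administrator will inform the rTMS provider of the patient’s assigned site (left DLPFC or a customized site) for rTMS treatment".
- **What is claimed** (Single-Blind Design): "A single-blind design will be maintained", and, for the statistician, "The biostatistician will be blinded to group".

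The same section says that researchers know the treatment order, because every participant has sham before active stimulation.

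**The concern.** One role, called the biostatistician in both sections, is the source of the allocation scheme and is also said not to know the allocation. The article keeps the recipient of the scheme away from procedures and analyses, so it recognises that holding the list and analysing the data should be separated. That safeguard covers the recipient of the list but not its source.

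At stake is the credibility of the comparison between sites. The Hypothesized Principal Findings section predicts a result in favour of the customized site. The trial is a small pilot, stated not to be powered for this phase, so a modest analytic choice could move the estimate. Self-reported outcomes do not remove the concern, because these choices come after the outcomes are collected. A reader of the article would credit the trial with a blinded analyst, and the described workflow does not support that credit.

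**Working it through.** No arithmetic bears on this point, and the article gives no figure to reproduce. The check is whether the two statements can both be true.

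**Step 1: what the holder of the scheme knows.** The scheme maps position in the sequence to group: "ensuring an equal number of participants—assigned sequentially—in each of the 2 groups". With sequential assignment, the k-th veteran randomised receives the k-th entry. An uncoded list plus the order of entry therefore gives the site of every participant.

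**Step 2: three ways to read the workflow.**

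| Reading | Provides the scheme | Blinded to group | Stated in the article? |
|---|---|---|---|
| Uncoded list, one biostatistician | True | False | Uncoded form not stated |
| List in labels A/B, key held only by the administrator | True | True | No code or key mentioned |
| Two statisticians, one for the list and one for the analysis | True of one | True of the other | No second statistician mentioned; both sections use the definite singular |

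The claim fails under the first reading and holds under the other two. The text neither states nor excludes the coded list. Its singular wording counts against the two-statistician reading.

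**Step 3: where knowledge of the site could act.**

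- *Data Preparation*: the imputation technique is left open, and all but one of a set of highly correlated alcohol-related measures are dropped, with no cut-off and no rule for which one stays.
- *Covariates*: candidates are kept if significantly associated with the outcome. The group label is not an input, so this route is weak, although the candidate list is given only as examples.
- *Confounders*: the list is again given as examples, and weights are inverse probabilities. On the natural reading these are probabilities of treatment site given the confounders, so group enters directly and the choice of confounders changes the weights.
- *rTMS Parameters*: missed sessions and gaps between sessions are potential covariates, which leaves one more choice.

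**Step 4: does the analysis need the real site names?** No. The mixed models for both objectives and the weighting model need to know which participants share a group, not which group is which site. Labels A/B are enough until the results are unmasked.

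**Result.** The statements are reconcilable only through an arrangement that the article does not describe.

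**The case against.** The strongest reply is that the two sections are compatible. If the list is in coded labels and the administrator holds the key, the biostatistician can provide the scheme and remain blinded. Describing the administrator as the *single* unblinded person points that way, since it implies that the biostatistician is not unblinded. A journal article also commonly leaves key custody to the full protocol or the analysis plan, and neither is shown here.

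Much of this stands. It rules out several stronger conclusions that a reader might infer:

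- **That analyst blinding does not exist.** This would require an uncoded list, which no section states.
- **That the biostatistician produces the list.** The article says only that the biostatistician provides it, and describes its development in the passive.
- **That the trial relies on analyst blinding.** It is presented as single-blind. Its masking effort is aimed at participants (placebo coil, headphones, simulated sensation, cap and navigation at every session), and the outcomes are their own reports.
- **That the analyst is the last safeguard because researchers are unblinded.** They are stated to know treatment order, which is the same for everyone. That is not knowledge of site. Only the rTMS provider is said to be told the site.

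The reply does not dispose of the conflict. The absence of a described mechanism would not by itself be a finding. Here, however, the article makes a positive blinding claim and describes a workflow that, on its face, undercuts it. The word *single* signals an intention without saying how it is met.

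**Conclusion.** The point holds in this form: the two sections conflict as written, and analyst blinding is asserted but not secured. It should be corrected, but it does not invalidate the trial.

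**Size.** The scheme covers every randomised veteran, with a target of up to 46. That describes the reach of the problem and is not a measure of bias. The bias, if any, cannot be derived from the document. It would act only through the choices left open at the analysis stage, chiefly imputation, removal of correlated measures and confounder weighting.

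**Assumptions.** First, the biostatistician performs or directs the analysis; the article does not say so, but the blinding statement would have little purpose otherwise. Second, no arrangement outside the article already codes the list or splits the roles. If one does, a sentence describing it settles the matter.

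**What to change.** Reconcile the two sections by one of these routes:

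1. **Coded list.** The biostatistician issues the list in labels A/B. The unblinded administrator alone decides which label is which site and holds that key until the dataset, covariates and model are locked. The analysis file carries only the labels and no field that reveals the site.
2. **Separate person.** Someone with no analysis role generates the list and hands it over. The analysing biostatistician sees only masked labels until the same lock.
3. **Drop the claim.** Delete the statement that the biostatistician is blinded.

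Routes 1 and 3 cost a sentence or two of wording; route 2 also needs a short task from another person. None changes the design, the sample size or the planned models.

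Timing matters for routes 1 and 2. The Results section reports that in June 2025 the 27 veterans who had completed the first phase were still awaiting the randomised phase, so at that date the change could precede the first allocation. If the biostatistician has since held an uncoded list, coding it later cannot restore that person's blinding. The remaining options are then an analyst who has not seen the list, or route 3.

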#### rTMS Device and Blinding Procedures

Sham and active rTMS will be delivered with the MagVenture MagPro X100 with MagOption stimulator and MagVenture Cool B65 A/P (active or placebo [aka sham]) coil, which can be switched to active or placebo. The coil is identical visually for both the sham or placebo and active conditions. During rTMS, veterans and researchers will wear headphones connected to the placebo noise generator so that they hear active TMS for both conditions, thereby maintaining the single-blind design. For sham rTMS, the coil will be switched to placebo or sham where a sensation is produced via surface electrodes placed on the forehead that mimics the sensation produced by the active coil. Thus, the sham rTMS looks, sounds, and feels similar to active rTMS.

#### Safety Measures

All investigators and research team members who will be providing the experimental treatment will undergo mandatory training on the use of the MagVenture device and the provision of active and sham rTMS.

In addition, to monitor for discomfort or pain, participants will be asked, after each rTMS session, to rate their pain. They will characterize the sensation by describing it as painful, tingling, sharp, piercing, tugging, pinching, or intolerable and rate the degree of the sensation on a scale ranging from 0 100 (100 being the worst pain you have experienced).

The rTMS treatment day safety monitoring plan and log will also be completed for each session. Each item in this log specifies whether it will be completed before, during, or after the rTMS session. The rTMS treatment day safety monitoring plan and log contains a customized severity indicator scale. For each safety variable specified in the rTMS treatment day safety monitoring plan and log, change from baseline is rated according to severity; and for each severity rating, there is a specified medical response to be followed. The ratings are on a scale ranging from 1 to 5, with a higher number indicating more deleterious change. This scale rates changes from baseline in vital signs (temperature, blood pressure, heart rate, and oxygen saturation levels), fatigue, tinnitus, sleep, dizziness, nausea, vomiting, confusion, seizure, syncope (fainting), headache, neck pain, skin integrity of the scalp, substance use, and mental health symptoms. This scale will be completed for each TMS session.

Participants will be clinically monitored for seizure by trained research staff. In the highly unlikely event that a seizure occurs, the following response plan will be followed:

A research team member will activate the emergency code for the Edward Hines Jr VA Hospital rapid response team (RRT).Trained research staff will assess the participant’s airway, breathing, and circulation.Upon arrival, the RRT will take over; assess; and treat the participant, if needed.The RRT will transport the participant to the Edward Hines Jr VA Hospital ED; for participants treated at a local VA ED, the PI will contact the participant within a week and encourage them to follow up with their primary care physician, in accordance with local VA policy, which recommends that patients treated in the ED should follow up with their primary care physician within 2 weeks.Any seizure will result in stopping treatment and withdrawal from the study.

An adverse event log will also be completed as necessary. In addition, an adverse event tracking log has been developed for this project. Both logs are integrated into the safety monitoring procedures of this study. All serious and nonserious adverse events will be documented in the adverse event tracking log.

All female participants will complete pregnancy tests. If a pregnancy test is positive, the participant will be discontinued from the study.

To ensure that participant medications remain stable during study participation, participants will be asked before each TMS session whether their medications have changed. In addition, medication lists will be reviewed once per week with the participant to monitor for any changes.

Any C-SSRS score of >3 will prompt a VA comprehensive suicide risk evaluation. If a participant scores >3 on the C-SSRS at any time, the VA suicide prevention team will be alerted, and either a member of the team or a trained member of the research team will complete the comprehensive suicide risk evaluation with the participant, as well as develop a suicide safety plan (if one has not been created by the participant within the past year). This information will be urgently shared with the veteran’s current mental health providers, if applicable. If the participant does not have current mental health providers, they will be offered an appointment with the mental health intake team or brought to the ED, as appropriate.

Participants will complete the Beck Depression Inventory-II; item 9 specifically assesses suicidal ideation, plan, and intent on an increasing point value scale (0-3; Table 3). To monitor for changes in suicidality, item 9 from the BDI II will be administered every week in accordance with our data safety monitoring sheet.

**Table 3 table3:** Beck Depression Inventory-II item 9: suicidal thoughts or wishes.

Scores	Responses
0	I don’t have any thoughts of killing myself.
1	I have thoughts of killing myself, but I would not carry them out.
2	I would like to kill myself.
3	I would kill myself if I had the chance.

Participants positively endorsing ≥2 indicators (more than transient ideation with possible plan and intent) will be queried about their response before proceeding with the screening. The assessor will be trained in risk assessment, which will include a review of the frequency and severity of suicidal ideation, a discussion of past and present planning behaviors, and current intent to act on ideation and planning.

A data safety monitoring board was not required by our study sponsor because this is a single-site pilot study.

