**Conclusions:**

We will be able to provide preliminary evidence of the efficacy, safety, and feasibility of a novel TMS target for veterans with AUD+mTBI.

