#### Baseline, Post–Sham rTMS, Post–Active rTMS, 2-Week, 1-Month, 3-Month, and 6-Month Follow-Up Visits

All veterans will complete the primary outcome measure: the WHO Disability Assessment Schedule (WHODAS 2.0), a self-report of functional disability. The following ARCs will also be collected as secondary outcomes: the Penn Alcohol Craving Scale, the Obsessive-Compulsive Drinking Scale, the Timeline Follow-Back (including the number of days between baseline and screening visits), and the Alcohol Craving Questionnaire. The following additional secondary outcomes will also be assessed: the Neurobehavioral Symptom Inventory, the PTSD Checklist for *DSM-5*, the Beck Depression Inventory-II, the Beck Anxiety Inventory, and the Mood and Anxiety Symptom Questionnaire. The C-SSRS will be repeated at baseline, after both sham and active rTMS treatment session 5, and at post–sham rTMS and post–active rTMS visits. We will also assess self-reported smoking status (ie, current, former, or never smoker, with never smoker defined as having smoked <100 cigarettes in a lifetime) and the Fagerström Test for Nicotine Dependence.

Finally, all female participants will complete a urine pregnancy test using a test kit at baseline and post–sham rTMS time points.

We will be using the VA REDCap (Research Electronic Data Capture; Vanderbilt University) secure web application for data collection and data entry. Data will be checked for completeness at the time of assessment and again at the time of data entry. Reasons for missingness will be documented.

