#### Statistical Approach

#### Objective 1

A within-participant, longitudinal design will be used in which all veterans will first receive sham rTMS followed by active rTMS applied to the customized neural target and the standard FDA-approved treatment site (left DLPFC). Thus, there will be 2 groups. The primary outcome, functional disability (WHODAS 2.0), will be assessed at baseline, after sham rTMS, and after active rTMS. A mixed effects model, incorporating within-participant correlation from repeated measures, will be used to compare the difference between difference between sham (Figure 4: PS-BL) and active rTMS (Figure 4: PA-PS) treatments. We will compare the aforementioned difference in sham and active rTMS of the left DLPFC neural target or site of stimulation with the customized neural target group.

#### Objective 2

A recovery curve will be constructed based on repeated functional disability (WHODAS 2.0) measures at post–active rTMS, 2-week, 1-month, 3-month, and 6-month follow-up time points (Figure 4: PA, F1–F4). A mixed effects model (incorporating within-participant correlation from repeated measures) will be used to examine change (using the slope of the model) in WHODAS 2.0 from post–active rTMS to each follow-up time point for each group. We will examine the change in slope of the left DLPFC group compared to the customized neural target group using WHODAS 2.0 measures from post–active rTMS to each follow-up time point.

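### The seizure and pregnancy rules end study participation as well as stimulation, so obtainable questionnaire outcomes after a post-randomisation event would not be collected

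*Protocol article*

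**What the plan says.** Two rules stand under Safety Measures. For a seizure: "Any seizure will result in stopping treatment and withdrawal from the study". For pregnancy: "If a pregnancy test is positive, the participant will be discontinued from the study". The section on the baseline to 6-month visits adds that "all female participants will complete a urine pregnancy test using a test kit at baseline and post–sham rTMS time points".

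After a seizure, Safety Measures also provides for emergency care and, for those treated at a local VA emergency department, one further contact: "the PI will contact the participant within a week and encourage them to follow up with their primary care physician". On recording of events it says: "All serious and nonserious adverse events will be documented in the adverse event tracking log". No further contact is described after a positive pregnancy test.

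The primary outcome is the WHODAS 2.0, a self-report measure taken at baseline (BL), post-sham (PS), post-active (PA) and four follow-up visits (F1 to F4, to 6 months). Objective 2 depends on the later visits: "A recovery curve will be constructed based on repeated functional disability (WHODAS 2.0) measures at post–active rTMS", continuing through F4. The Abstract's conclusion is that "We will be able to provide preliminary evidence of the efficacy, safety, and feasibility of a novel TMS target".

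**The concern.** Ending stimulation and ending study participation are different decisions, and the seizure sentence names both. The first does not require the second, because the WHODAS 2.0 and the other questionnaires can be completed by someone who is no longer stimulated. The rule therefore gives up data that could be had.

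After a seizure the loss may be informative, for two reasons. Stimulation site is the randomised factor, so a seizure provoked by active stimulation would make missingness depend on treatment. The article's rationale section also describes a population at raised seizure risk through possible alcohol withdrawal, so a seizure may mark a change in drinking and function, which the trial measures. Data Preparation offers imputation by unnamed techniques. Whatever technique is chosen, values after the event would be extrapolated, and the trial's data could not test the assumption behind them.

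Safety is among the things the study intends to report, and the participant whose later course is most relevant would leave the scheduled assessments.

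**Working it through.** **1. Which visits are lost**

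| Event | Visits not collected | Consequence |
|---|---|---|
| Seizure in the sham block | PS, PA, F1 to F4 (6) | Neither the sham change (PS − BL) nor the active change (PA − PS) is observed |
| Positive post-sham pregnancy test | PA, F1 to F4 (5) | Active change and the whole recovery curve missing |
| Seizure in the active block | PA, F1 to F4 (5) | Active change and the whole recovery curve missing |
| Positive baseline pregnancy test | May precede randomisation | May simply apply the existing pregnancy exclusion |

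Objective 1 compares PA − PS with PS − BL, and Objective 2 uses only PA and F1 to F4. A participant in the second or third row therefore has no observed active-treatment change and no point on the recovery curve.

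**2. Does any passage keep these participants in follow-up?** Safety Measures, the visit section, Data Preparation and Statistical Approach were read together. None does. None says that data already collected are removed.

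**3. The plan's own sample size.** Inputs from Sample Size Justification: effect size 0.65, power 80%, type I error 5%, attrition 20%, result 46. Assuming a two-sided, two-group comparison of means:

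- n per group = 2 × (1.960 + 0.842)² / 0.65² = 37.2, rounded up to 38.
- 38 × (1 + 0.20) = 45.6, rounded up to 46, which matches; 38 / (1 − 0.20) = 47.5, rounded up to 48.

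On this reading 46 is one group of the target identification phase, which the article does not spell out. The present point does not depend on it and uses 46 only as the planned enrolment.

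**4. Weight of one withdrawal**

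- 1 / 46 = 2.2% of planned enrolment.
- 1 / 27 = 3.7% of the veterans awaiting the RCT phase in June 2025 (Results).
- 1 / 13.5 = 7.4% of an arm, only if enrolment stopped at 27 and was split equally.

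**5. How many withdrawals might occur.** The only indication of frequency is the phrase "In the highly unlikely event that a seizure occurs". With an assumed per-participant rate p, the expected number among 46 is 46p, and the chance of at least one is 1 − (1 − p)^46:

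| Assumed p | Expected number | Chance of at least one |
|---|---|---|
| 0.1% | 0.05 | 4.5% |
| 0.5% | 0.23 | 21% |
| 1% | 0.46 | 37% |
| 2% | 0.92 | 61% |
| 5% | 2.3 | 91% |

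These rates are assumptions that show a range; none comes from the document. For comparison, the planned 20% attrition is 0.20 × 46 = 9.2 participants.

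**The case against.** The strongest case on the other side has four parts, and much of it stands.

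- *Nothing is thrown away.* A reader might infer that these participants' data are discarded or that they are excluded from analysis. The article says neither. Later visits are not collected, earlier data are not said to be deleted, and imputation is planned. It is therefore not shown that the comparison as randomised is broken.
- *The safety event is captured.* A reader might infer that the trial stops observing people who have a seizure. The session log rates seizure, every adverse event goes into the tracking log, and a contact within a week is planned for those treated at a local VA emergency department. The count of seizures by arm would survive. What is shortened is later scheduled assessment. The article condenses a fuller protocol, so it cannot be concluded that no other safety follow-up exists.
- *Non-ignorable missingness is not demonstrated.* Dropout triggered by a recorded event is not automatically non-ignorable; that depends on whether the unseen WHODAS 2.0 values relate to dropout given what was recorded. Only the possibility can be claimed.
- *Pregnancy is different.* A positive post-sham test precedes any active stimulation and is not a treatment-related event. The argument about informative loss rests on seizure alone; for pregnancy the point is only that obtainable data are forgone.

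The defence does not reach the rule itself. Withdrawal from the study is stated in addition to the end of treatment, so this is not a detail left to another document.

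**Conclusion.** The point holds as a low-cost improvement to wording, not as an error that threatens the trial. The stated rules would lose five scheduled outcome visits, or six after a seizure in the sham block, for a participant who could still complete questionnaires. After a seizure that loss may be related to treatment or to drinking.

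The effect is probably small. Seizures are expected to be rare, one loss is 2.2% of 46 or 3.7% of 27, and the RCT phase is expressly an unpowered pilot. No sample size, power or type I error figure changes.

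The conclusion assumes that the post-sham pregnancy test falls after randomisation and that the full protocol does not override the article's wording. Whether stimulation should end after either event is a clinical matter and is not questioned here.

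**What to change.** Leave the rules for ending stimulation unchanged. For events after randomisation, replace withdrawal or discontinuation from the study with wording to this effect: a participant whose stimulation has ended is asked, if willing, to complete the remaining scheduled questionnaires (PS where still due, PA, F1 to F4) and adverse event follow-up, and is analysed in the arm to which they were randomised. Since stimulation would have ended, tie the dates of the later visits to a defined point, such as the planned end of treatment. State when randomisation occurs relative to the baseline pregnancy test; a positive test there may remain an eligibility exclusion.

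The cost is a short change to the protocol and consent form, made before RCT data collection begins (it had not begun as of June 2025), plus questionnaire visits for what is likely to be very few people. The downside is that values observed off treatment may slightly dilute the efficacy estimate.
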